## Abstract

**Background:**

Approximately 20-40% of outpatients with diabetes experience elevated levels of emotional distress, varying from disease-specific distress to general symptoms of anxiety and depression. The patient's emotional well-being is related to other unfavorable outcomes, like reduced quality of life, sub-optimal self-care, impaired glycemic control, higher risk of complications, and increased mortality rates. The purpose of this study is to test the effectiveness of a new diabetes-specific, mindfulness-based psychological intervention. First, with regard to reducing emotional distress; second, with respect to improving quality of life, dispositional mindfulness, and self-esteem of patients with diabetes; third, with regard to self-care and clinical outcomes; finally, a potential effect modification by clinical and personality characteristics will be explored.

**Methods/Design:**

The Diabetes and Mindfulness study (DiaMind) is a randomized controlled trial. Patients with diabetes with low levels of emotional well-being will be recruited from outpatient diabetes clinics. Eligible patients will be randomized to an intervention group or a wait-list control group. The intervention group will receive the mindfulness program immediately, while the control group will receive the program eight months later. The primary outcome is emotional distress (anxiety, stress, depressive symptoms), for which data will be collected at baseline, four weeks, post intervention, and after six months follow-up. In addition, self-report data will be collected on quality of life, dispositional mindfulness, self-esteem, self-care, and personality, while complications and glycemic control will be assessed from medical files and blood pressure will be measured. Group differences will be analyzed with repeated measures analysis of covariance.

The study is supported by grants from the Dutch Diabetes Research Foundation and Tilburg University and has been approved by a medical ethics committee.

**Discussion:**

It is hypothesized that emotional well-being, quality of life, dispositional mindfulness, self-esteem, self-care, and blood pressure will improve significantly more in the mindfulness group compared to the control group. Results of this study can contribute to a better care for patients with diabetes with lowered levels of emotional well-being. It is expected that the first results will become available in 2012.

**Trial registration:**

Dutch Trial Register NTR2145.

## Background

It has been estimated that worldwide, approximately 285.000.000 persons have diabetes mellitus (DM) and this number is expected to rise to 439.000.000 by 2030 [1]. This sharp increase in prevalence is partly due to the ageing of the population and the increase in the number of people having overweight and who are physical inactive [2]. DM is a chronic disease characterized by high levels of blood glucose resulting from a deficit in the secretion of the hormone insulin (absolute insulin deficiency: Type 1 DM), or insufficient insulin action (insulin resistance) and/or a failure of the beta-cells to produce enough insulin, i.e. beta-cell dysfunction (Type 2 DM)[3]. Type 2 DM is the most frequent form, prevalent in approximately 90% of the cases [4]. For all patients with diabetes, appropriate glycemic control by means of adequate self-management is required in order to prevent or delay the development of diabetes complications: macrovascular complications (e.g. coronary artery disease) and microvascular complications (i.e. nephropathy, retinopathy, and neuropathy). This self-management consists for example of a healthy diet, physical exercise, frequent assessment of the blood glucose levels, and (in many cases) the use of medication to control the blood glucose (an oral hypoglycemic agent and/or insulin)[3].

A considerable proportion of the patients with diabetes (20-40%) experience emotional problems, which vary from disease-specific worries (such as fear of hypo's or worries about complications) to more general symptoms of distress, anxiety and depression [5-7]. These problems are not only unpleasant for the persons experiencing them, but studies show also that co-morbid emotional distress in patients with DM is associated with reduced quality of life [8], poor self-care behaviors [9], more negative appraisals of insulin therapy [10], reduced glycemic control [9] and subsequent adverse cardiovascular outcomes, and even mortality [8,11].

Despite the fact that emotional distress is so common in patients with diabetes, the attention for emotional problems in both practice and research is still limited. In practice, the recognition rates of emotional problems by clinicians are low and so are treatment rates [12]. Similarly, in the field of diabetes research, studies that test psychological interventions to improve the emotional well-being in patients are scarce. In addition, those studies that have been conducted often have important limitations, such as lack of controlled designs and small sample sizes [13]. However, it is true that the attention for emotional problems in DM patients is increasing since the last decade. In practice, screening for emotional problems is recommended in the latest versions of the standards of care of the International Diabetes Federation [14] and the American Diabetes Association [15]. In addition, in research, there are more and more studies examining the effectiveness of psychological interventions on clinical depression. Anxiety symptoms and diabetes-specific emotional distress have received, however, much less attention in diabetes research.

The results of well-designed studies that have been conducted to test psychological interventions in diabetes patients with emotional problems show that cognitive behavioral therapy is an effective treatment for major depression in diabetes patients [16] and a potentially effective treatment in reducing symptoms of anxiety, perceived stress, and diabetes-specific emotional distress [17,18]. Another promising psychological intervention that may help to reduce symptoms of depression, anxiety, and diabetes-specific emotional distress is based on the cultivation of mindfulness. Mindfulness can be defined as the self-regulation of one's attention focusing on direct experience, while adopting a curious, open, and accepting attitude towards these experiences, especially one's psychological processes, such as thoughts and feelings [19]. Mindfulness-based interventions can be considered promising as positive effects of mindfulness programs on emotional well-being and quality of life have been reported in diverse patients groups, like chronic pain patients and patients with cancer [20-22]. In addition, research has shown that the program is beneficial for patients with recurrent depression. In these patients, the intervention appeared to be superior to traditional cognitive behavioral therapy in the prevention of relapse of depression [23]. While in a recent meta-analysis, mindfulness-based interventions have been found to have medium to large effects regarding the reduction of symptoms of anxiety and depression [24], only two studies have focused on the effects of a mindfulness program on patients with diabetes. These studies showed that the interventions resulted in improved emotional well-being (Cohen's *d *= 0.86 for depressive symptoms and 0.43 for anxiety) [25], improved self-care behaviors (Cohen's *d *= 0.68)[26] and decreased HbA_1c _values (Cohen's *d *= 0.46) [25] (Cohen's *d *= 0.35)[26]. However, only one of the two studies was a randomized controlled trial, but this study did not include emotional well-being as an outcome measure [26]. Therefore, there is a clear need for randomized controlled studies in this area, examining the potential benefits of mindfulness interventions on emotional well-being in patients with DM.

In addition to the potential contribution of mindfulness to emotional well-being, mindfulness may also have a beneficial influence on self-management in DM patients. First, because mindfulness interventions enhance emotional well-being, and a better mood is associated with better self-care behavior, mindfulness is expected to enhance self-care behavior as well. Second, mindfulness improves one's ability to behave oneself constructively in harmony with his/her values, even during the experience of difficult thoughts and emotions [27]. Finally, because considerable focus is placed on bodily sensations during mindfulness interventions, mindfulness leads people to become more in touch with their body and its signals and needs [28], which is expected to lead to better self-care.

A positive effect of a mindfulness intervention may also be expected on blood pressure. It is known that episodic or chronic emotional distress can increase blood pressure [29]. This is unfavorable for patients with diabetes, as the prevalence of high blood pressure in people with diabetes is approximately twice as high compared to the general population [30] and both diabetes and high blood pressure are important risk factors for cardiovascular disease [30]. To date, only two studies have examined the influence of mindfulness on blood pressure, finding a reduction in mean arterial pressure in DM patients [25] and a reduction in resting systolic blood pressure in normotensive students [31].

If the mindfulness intervention appears to be effective in reducing emotional distress in DM patients, it is useful to know which patients will most likely benefit from the intervention. However, research into differences in effectiveness of the intervention between groups of patients with different characteristics (e.g. differences in personality and demographic and medical characteristics) is scarce.

### Objectives and hypotheses

Because of the paucity of studies on the effectiveness of psychological interventions for emotional problems in DM patients, especially regarding mindfulness based interventions, the purpose of this study is to test the effectiveness of a mindfulness-based psychological intervention. The primary outcome is emotional distress (symptoms of depression, anxiety, diabetes-specific stress, and general perceived stress). Secondary outcomes are quality of life, (diabetes-specific) mindfulness, and self-esteem, and our tertiary outcomes are self-management, glycemic control, and blood pressure. Finally, we will examine which patient characteristics (like the extent of complications and personality) predict which patients most likely benefit from the intervention.

With regard to our first outcome measure, we hypothesize that after an eight-week mindfulness-based training DM patients will experience significant greater reductions in emotional distress (diabetes-specific stress, anxiety, and depressive symptoms) compared to a wait-list control group. Concerning our secondary outcome measures, we hypothesize that the intervention will lead to greater improvements in psychological quality of life, dispositional (diabetes-specific) mindfulness, and self-esteem compared to a wait-list control group. In addition, we expect, consistent with two other studies [32,33], that changes in dispositional mindfulness will mediate the hypothesized effects of the intervention on above mentioned outcomes. Regarding our tertiary, more clinical, outcome measures, we hypothesize that the intervention will lead to better diabetes self-care, lower HbA_1c_, and lower BP in people with elevated BP. Finally, we are interested in personality and clinical factors that could possibly act as effect modifiers. We do not have clear expectations about the direction of the possible influence of these characteristics, being complications (yes/no), diabetes type (DM1 versus DM2), co-morbidity (yes/no), and personality.

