### Outcome parameters

#### 1. Primary outcome measures

##### Stress, anxiety and depressive symptoms

We will include the Hospital Anxiety and Depression Scale (HADS) to measure symptoms of anxiety (HADS-A: e.g., "Worrying thoughts go through my mind") and depression (HADS-D: e.g., "I feel as I am slowed down") in DM patients [37]. The self-report scale consists of 14 items, answered on a 4-point Likert scale, with the HADS-A and HADS-D both comprising 7 items (*0-3*). The score range for the anxiety and the depressive symptoms subscales is 0 to 21. The HADS has been validated in the general population and in somatic and psychiatric patients [38,39]. It has been shown to be a valid and reliable instrument with Cronbach's α ranging from 0.67 to 0.93 for the two subscales [37-39].

The Dutch version of the Perceived Stress Scale (PSS) will be included to measure general perceived stress (the degree to which situations in one's life are appraised as stressful) (e.g. "In the last month, how often have you felt nervous and stressed?"). It has been shown to be a reliable measure with Cronbach's α ranging from 0.84 to 0.86 [40]. The present version consists of 10 items which are answered on a five-point Likert scale, ranging from 'never' to 'very often' *(0-4) *[41].

The short Dutch version of the Profile of Mood States (POMS) [42] will be used to assess transient, fluctuating mood states. The scale consists of 32 adjectives about positive and negative mood states which have to be rated on a five-point Likert scale *(0 = not at all, 4 = very much) *based on how well each item describes one's mood during the last couple of weeks. For the interpretation of the results the items are divided into five subscales: Tension-anxiety (6 items); Depression-dejection (8 items); Anger-hostility (7 items); Vigor-activity (5 items); and Fatigue-inertia (6 items). The scale has sufficient consistency reliability and construct validity, with Cronbach's α's of the five subscales varying between 0.82 and 0.91 [42,43].

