##### Diabetes specific emotional problems

We will include the Dutch version of the self-report questionnaire Problem Areas in Diabetes Survey (PAID), which consists of 20 statements about common negative feelings related to living with diabetes (e.g., "Feeling depressed when you think about living with diabetes", "feeling discouraged with your diabetes regimen") [44]. The items are rated on a six-point Likert scale *(1 = not a problem, 6 = a serious problem)*. PAID scores are transformed to a 0-100 scale, to facilitate interpretation [45]. A higher score indicates more emotional distress, with a cut-off score of 40 indicating seriously elevated emotional distress [46]. Factor analysis revealed that the factor structure can be represented by a one factor model (PAID total: emotional adjustment) and a four factor model (subscales: emotional problems, treatment problems, food problems, and lack of social support) [45]. We will examine the results with both models. The survey has proven to be a reliable measure, with a Cronbach's α of 0.95 for the one factor model. For the four factor model the Cronbach's α's are in range of 0.93 (emotional problems), 0.74-0.76 (treatment problems), 0.70-0.74 (food problems), and 0.69-0.72 (lack of social support) [45]. In addition, research in Dutch and American patients found support for convergent and discriminative validity of the PAID [45,47].

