#### Planned analyses

Repeated measures analysis of variance ((M)ANCOVA) will be used to test the hypotheses concerning the differences between groups on the dependent variables over time. In these tests age, sex, and co-morbidity will be included as covariates, in addition to those other potentially confounding variables that will show an at least marginally significant (p < .10) difference between groups. The analyses concerning the subgroup effects will be conducted on the sample as a whole, whereby possible moderating variables, like complications and personality will be included in the analyses as between-subjects factors. All analyses will be based on the intention-to-treat approach.

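### The primary outcome is not one defined endpoint: its content differs between sections, up to 13 scores sit under it, and no stated rule says which of them decide success at 0.05

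*Protocol article*

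**What the plan says.** The protocol article describes the primary outcome in four places.

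- Abstract, Methods/Design: "The primary outcome is emotional distress (anxiety, stress, depressive symptoms". Its data are those "for which data will be collected at baseline, four weeks, post intervention, and after six months follow-up".
- Objectives and hypotheses, the objective: "The primary outcome is emotional distress (symptoms of depression, anxiety, diabetes-specific stress, and general perceived stress".
- Objectives and hypotheses, the hypothesis for the first outcome, set after the eight-week training: "significant greater reductions in emotional distress (diabetes-specific stress, anxiety, and depressive symptoms) compared to a wait-list control group".
- Outcome parameters, primary outcome measures: HADS (anxiety and depression subscales), PSS, POMS and PAID. For POMS, "For the interpretation of the results the items are divided into five subscales": tension, depression, anger, vigor and fatigue. For PAID, a one-factor total and a four-factor set of subscales are described, and "We will examine the results with both models".

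The sample size section gives one alpha of 0.05, a power of 0.80, a medium effect and 80 patients per arm who are to be included and complete the study. The planned analysis is: "Repeated measures analysis of variance ((M)ANCOVA) will be used to test the hypotheses concerning the differences between groups on the dependent variables over time". No primary score, primary time or order of testing is named.

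**The concern.** The primary outcome decides whether the intervention is called effective. Here the sections disagree on what it contains. A significant PSS result is primary under the objective but not under the hypothesis. A significant POMS vigor or fatigue result is primary under the outcome section but matches no construct in the objective. With no stated success rule, the score that counts can be chosen after the data are seen, and all of these choices would be consistent with some part of the text.

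POMS tension and depression also overlap with HADS-A and HADS-D, so two constructs each have two candidate scales. If success means any one primary score significant at 0.05, the trial-level error rate is above 0.05, and the power statement describes one comparison rather than this family.

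**Working it through.** **1. The lists side by side.**

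| Place | Depression | Anxiety | Diabetes-specific stress | General perceived stress | Other mood |
|---|---|---|---|---|---|
| Abstract | yes | yes | only 'stress', unspecified | only 'stress', unspecified | no |
| Objective | yes | yes | yes | yes | no |
| Hypothesis | yes | yes | yes | no | no |
| Primary measures | HADS-D, POMS depression | HADS-A, POMS tension | PAID | PSS | POMS anger, vigor, fatigue |

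The abstract can be read as agreeing with the objective. The hypothesis cannot, and three POMS subscales lie outside every list of constructs.

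**2. Count of scores under the primary heading.** HADS 2 + PSS 1 + POMS 5 + PAID (1 total + 4 subscales) = 13. The objective's four constructs, with one score each, give 4.

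**3. Number of tests.** A repeated measures analysis gives one group-by-time test per score, so I count one test per score and do not multiply by the three post-baseline times.

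**4. Chance of at least one false positive**, each score at two-sided 0.05, no true effect.

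- Independent scores: 1 − 0.95^k. For k = 4: 1 − 0.8145 = 0.185. For k = 13: 1 − 0.5133 = 0.487.
- Independent, in favour of the intervention only: 1 − 0.975^k. For k = 4: 0.096. For k = 13: 0.280.
- Correlated scores: equicorrelated normal test statistics with threshold 1.96. The document gives no correlations, so 0.5 and 0.7 are assumptions.

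| Correlation | 4 scores, any | 4 scores, favouring intervention | 13 scores, any | 13 scores, favouring intervention |
|---|---|---|---|---|
| 0 | 18.5% | 9.6% | 48.7% | 28.0% |
| 0.5 | 15.6% | 7.8% | 33% | 16.7% |
| 0.7 | 13.0% | 6.5% | 24% | 12.0% |
| Nominal, one test | 5% | 2.5% | 5% | 2.5% |

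**5. The stated sample size.** Taking the medium effect as d = 0.5 (no figure is given), a two-sided t-test at 0.05 with power 0.80 needs 64 per arm, and 64 / 0.80 = 80 if 20% attrition is assumed. That reaches 160, but neither assumption is in the document, which asks for 80 per arm to complete. I therefore use 80 completers per arm below.

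**6. Power for one score at 80 per arm, d = 0.5** (noncentral t; with baseline adjustment the effect becomes d / √(1 − r²), where r is the assumed baseline-to-outcome correlation).

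- At 0.05, unadjusted: 0.88.
- At the first Holm threshold for four scores, 0.05 / 4 = 0.0125, unadjusted: 0.74.
- At 0.0125, r = 0.5: 0.5 / √0.75 = 0.577, power 0.87.
- At 0.0125, r = 0.6: 0.5 / √0.64 = 0.625, power 0.92.

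**The case against.** The other side has several sound points.

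- This is a journal article, and a multiplicity rule may sit in an analysis plan that is not shown. A reader might infer that the trial has no error control. The text supports only that none is stated. The notation (M)ANCOVA also leaves room for a multivariate test as a gate, although the article does not call it one or say which scores would enter it.
- Thirteen is an upper bound. Forming POMS subscales for interpretation and looking at two PAID models is not the same as declaring each score a confirmatory test, and PAID total shares its items with its subscales.
- A reader might multiply 13 scores by three times to get 39 tests. The planned repeated measures analysis does not do that.
- A reader might conclude that a false claim of effectiveness is likely. With one test per score no figure above reaches 50%, and the part that favours the intervention is about half the total.
- POMS is an instrument and the lists name constructs, so its absence from them is not by itself a contradiction. Two of its subscales do measure listed constructs.
- Testing over all time points with follow-up contrasts is legitimate. Making week 8 the sole primary contrast is partly a design choice.

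These points limit the size of the problem. They do not remove it: the objective and the hypothesis differ within one section, anger, vigor and fatigue are placed under primary without belonging to any stated construct, and an unseen plan cannot make these parts of the document agree.

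**Conclusion.** The point holds in this form: the primary set is inconsistent within the article, up to 13 scores are placed in it, and one alpha of 0.05 comes with no stated rule for success. If any single significant score counts, the error rate is about 13-19% for the four constructs of the objective and 24-49% for all 13 scores. For false results in favour of the intervention it is about 7-10% and 12-28%, against 2.5%. These ranges assume equal correlations from 0.7 down to 0 and one test per score. The size depends on those assumptions, but every case tried is above the nominal level. The inconsistency itself depends on no assumption.

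**What to change.** - Use one primary set in the abstract, the objective, the hypothesis and the primary-measures section. The four constructs of the objective are a natural choice: HADS-A, HADS-D, PSS total and PAID total.
- Move the five POMS subscales and the four PAID subscales to secondary.
- Test the primary set with Holm at a family-wise 0.05, or state that a multivariate test over exactly this set is the gate.
- Name the primary contrast. The baseline-adjusted group difference at T3 (week 8) matches the hypothesis about the effect after training; T2 and T5 would then be secondary.

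The cost is wording and one testing step. The downside is power: for one score at the first Holm threshold it is 0.74 unadjusted, against 0.88 at 0.05, with the stated 80 completers per arm and d = 0.5. Baseline adjustment at r = 0.5-0.6 brings it to 0.87-0.92, so the planned size can carry the change if those assumptions hold and 80 per arm do complete. The Discussion reports 16 patients enrolled at the time of writing, so the change could be made before outcome data could influence it.
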